## Abstract

**Background:**

Chemotherapy-induced peripheral neuropathy (CIPN) is a common and clinically relevant side effect of chemotherapy. Approximately 50% of all leukemia, lymphoma, colorectal- and breast cancer patients are affected.

CIPN is induced by neurotoxic chemotherapeutic agents and can manifest with sensory and/or motor deficits. It is associated with significant disability and poor recovery. Common symptoms include pain, altered sensation, reduced or absent reflexes, muscle weakness, reduced balance control and insecure gait.

These symptoms not only affect activities of daily living, subsequently reducing patients’ quality of life, they have far more become a decisive limiting factor for medical therapy, causing treatment delays, dose reductions, or even discontinuation of therapy, which can affect the outcome and compromise survival. To date, CIPN cannot be prevented and its occurrence presents a diagnostic dilemma since approved and effective treatment options are lacking.

Promising results have recently been achieved with exercise. We have revealed that sensorimotor training (SMT) or whole body vibration (WBV) can reduce the symptoms of CIPN and attenuate motor and sensory deficits. We furthermore detected a tendency that it may also have a preventive effect on the onset of CIPN.

**Methods:**

We are therefore conducting a prospective, multicentre, controlled clinical trial involving 236 oncological patients receiving either oxaliplatin (*N* = 118) or vinca-alkaloid (N = 118) who are randomized to one of two interventions (SMT or WBV) or a treatment as usual (TAU) group. Primary endpoint is the time to incidence of neurologically confirmed CIPN. Secondary endpoints are pain, maintenance of the functionality of sensory as well as motor nerve fibres as well as the level of physical activity. The baseline assessment is performed prior to the first cycle of chemotherapy. Subsequent follow-up assessments are conducted at 12 weeks, after completion of chemotherapy, and at a 3-month follow-up. Patients who develop CIPN receive an additional assessment at this time point, as it represents the primary endpoint.

**Discussion:**

We hypothesize that SMT and WBV prevent the onset or delay the progression of CIPN, decrease the likelihood of dose reductions or discontinuation of cancer treatment and improve patients’ quality of life.

**Trial registration:**

Deutsche Register Klinischer Studien (DRKS00006088, registered 07.05.2014).

## Background

Chemotherapy-induced peripheral neuropathy (CIPN) is caused by neurotoxic agents in cancer therapy. Oxaliplatin and vinca-alkaloids are two of the main agents responsible for CIPN. Oxaliplatin inhibits DNA synthesis and repair due to its ring structure, which causes the death of neural cells. Vinca-alkaloids cause axonal damage and disrupt axonal transport via microtubular damage. The main cancer patients affected by oxaliplatin are colorectal, NHL and breast cancer patients, while lymphoma patients but also ALL and pulmonary cancer patients mainly receive vinca-alkaloids. Peripheral sensory nerves are especially sensitive to toxins. Damage caused to these fibres leads to various sensory and motor dysfunctions. Patients suffer from symptoms such as loss of sensation, apparent as numbness, tingling or burning, dysaesthesia, reduced or absent Achilles tendon reflexes [1, 2] pain, and loss of balance control leading to instable gait, as well as an increased incidence of accidents and falls [3].

Even though CIPN is such a prevalent and clinically relevant side effect [4], not only diminishing patients’ quality of life, but also leading to treatment delays, dose reductions or even discontinuation of therapy, affecting the outcome and compromise survival [5], little research has been done to investigate the potentially beneficial effects of specific exercises to counteract the various motor and sensory dysfunctions.

To date, CIPN cannot be prevented and there is no consent regarding the treatment of CIPN. Research has focused on pharmacological therapies aimed at reducing CIPN or treating selected side effects while [6–8] this has been helpful for neuropathic pain, it does not address the many other side effects of CIPN [9–12]. On the contrary, many of these agents have been shown to have additional negative side effects [13]. An exercise intervention has now revealed promising results. In a first clinical trial, we [14] conducted an exercise intervention consisting of endurance, strength and sensorimotor training (SMT) twice a week for 36 weeks, accompanying lymphoma patients from diagnosis to completion of treatment. The study revealed a significant reduction of neuropathic symptoms. Patients exercising were able to reduce CIPN-related symptoms (e.g., peripheral deep sensitivity) by 87%, while in the control group no change (0%) was detected. After 36 weeks, 55% of the control group still had symptoms related to CIPN while only 4% remained with CIPN in the intervention group.

Furthermore, a positive tendency regarding the incidence of CIPN could be detected. Unfortunately, the sample size was too small in this study to show significant results. The majority of expertise on exercise and peripheral neuropathy (PNP) arises from research on patients with diabetic neuropathy. In a systematic review [15], we evaluated all exercise intervention studies for neuropathic patients independent of the cause. We found that for toxically induced PNP such as CIPN, balance exercises were most beneficial for motor as well as sensory symptoms.

Taking previous findings into consideration, this strengthened our presumption that SMT played a decisive role in the study by Streckmann et al. [14], as studies in healthy adults have revealed that SMT has the potential to counteract some of the mentioned side-effects of PNP. SMT is characterized by functional adaptations of the neuromuscular system [16, 17], regeneration of neuromuscular structures [18] and the diminished prevalence of injuries [19, 20], leading to improved proprioception [17], intermuscular coordination and balance control, causing fewer falls [21] and increasing mobility. Furthermore, studies with strength training alone or in combination with endurance training showed little to no significant intergroup differences. In line with these findings, Steimann [22] and Vogt [4] evaluated the subjective effectiveness of physiotherapy (gait training and balance exercises) and ergotherapy (e.g., walking on granulate material), while Steimann also looked at electrotherapy. Both found that patients experienced ergotherapy and physiotherapy as very helpful. One case report on a breast cancer patient, suffering from painful CIPN, showed improved balance after balance training [23].

Targeting similar mechanisms as SMT, though possibly addressing different sensory qualities, whole body vibration (WBV) has also been taken into consideration. Previous studies investigating WBV have shown a positive impact on parameters influenced by the side-effects of PNP. Kawanabe et al. [24] and Bogaerts et al. [25] showed that elderly individuals improve their gait after vibration exercises. Rittweger [26] and Kirchner et al. [27] found WBV to have a positive impact on pain reduction, while further studies showed an effect on deconditioned skeletal muscle [28], improved isometric strength [26, 29, 30], postural sway [31] and reduced fall frequency [25]. Schönsteiner et al. [32], performed a multimodal exercise program containing WBV, massage and physical exercises with CIPN patients (*N* = 131), achieving less symptoms and pain, improved physical fitness and better coordination. Both SMT and WBV require very little time and effort, but have a high impact. Especially for cancer patients, this aspect plays an important role, as therapy can be very strenuous for the patients. Training and devices are feasible, meet the requirements of hospital hygiene and are portable for all phases of therapy, even in isolation. Training is therefore even possible during cytopenias, often a limiting factor for exercise interventions concomitant to therapy.

We therefore conducted a randomized, controlled, pilot study assessing cancer patients with neurologically confirmed CIPN to either SMT (*n* = 10), WBV (*n* = 10) or a control group (n = 10) with no intervention additionally comparing them to an age- and gender matched healthy control group (n = 10). WBV and SMT were feasible for patients with CIPN and both exercise groups benefited (improved reflex activity of the Achilles- and patella tendon), peripheral deep sensitivity and pain) from 6 weeks of intervention twice a week [33].

To summarize, there are no existing prevention trials assessing the potentially beneficial effects of exercise for the onset of CIPN and only very little is known about the effects of exercise on the symptoms of CIPN. Based on our previous findings as well as from practical experience with patients, we hypothesize that SMT and WBV prevent the onset of CIPN on the one hand and/or can influence the progress of CIPN and associated motor and sensory symptoms such as balance control, coordination and mobility, as well as sensitivity, proprioception and pain, enhancing patients’ quality of life and assuring the best clinical outcome by enabling patients to receive their planned therapy regimen.

## Methods/design

### Study participants and recruitment

We plan to enrol 236 newly diagnosed haematological/oncological patients who are scheduled to receive chemotherapy containing either oxaliplatin or a vinca-alkaloid, aged ≥18 years, with the mental and physical ability to provide signed informed consent and participate in the study. Patients are recruited at three participating centres: The University Hospital of Cologne, the St. Antonius Hospital in Eschweiler and the joint practice for oncology and hematology at the Sachsenring in Cologne. Exclusion criteria is a pre-existing neuropathy of other cause. Therefore, patients will be assessed clinically for signs of neuropathy and will undergo nerve conduction studies prior to randomization. Neuropathy will be defined electrophysiologically as CMAP amplitude below 5 mV, SNAP amplitude below 5 μV, and nerve conduction velocity below 40 m/s of tibial or sural nerve). Further exclusion criteria are previous therapies containing neurotoxic agents, any contraindication for whole body vibration (instable bone metastases, acute leg thrombosis, a fracture in the lower extremities in the past 2 years, foot ulcers, artificial hips or other osteosynthesis), and myocardial infarction, angina pectoris or heart disease (NYHA III-IV) within the past six months.

### Experimental design

The study follows a prospective, randomized controlled design, allocating patients to three groups: an intervention group receiving SMT, an additional intervention group receiving WBV, and a control group (Fig. 1). Patients in the two intervention groups receive a defined exercise program twice a week in addition to treatment as usual (TAU). Patients in the control group receive TAU and are given the opportunity to participate in the preferred intervention after completion of the study. The interventions and assessments take place at the respective centers.

Data is assessed at 3 to 5 measuring time points, depending on the length of medical therapy and a potential incidence of CIPN (Fig. 2 and Fig. 3). The baseline assessment (T0) is performed prior to the first cycle of chemotherapy. All patients are re-assessed after three months (T1). For most patients, this is simultaneously the post-therapy measurement (Tp) (Fig.2), while for patients who are treated for more than three months it represents an interim assessment (T1) (Fig.3), in order to ensure comparability regardless of the entity. These patients have an additional assessment upon completion of their medical therapy (~6 months). The follow-up measurement is performed three months after completion of chemotherapy (T2) in order to compensate for any potential coasting effects. Each assessment has a duration of 90 min at most. To ensure the detection of CIPN, patients are informed about possible symptoms of CIPN and asked to report back to the study coordinators immediately. Furthermore, patients are regularly asked for potential symptoms by their physicians. Additionally, a short neurological test battery is performed every 6 weeks. Sports therapists will be blinded and must not ask patients about CIPN symptoms during the interventions in order to obtain comparability with the control group. In case a CIPN is neurologically confirmed, patients are also tested at this time point (Ti).

**Fig. 1 Fig1:**
[figure not shown]
Overview of the study design

**Fig. 2 Fig2:**
[figure not shown]
Measuring time points for patients with 3 months of therapy

**Fig. 3 Fig3:**
[figure not shown]
Measuring time points for patients with more than 3 months of therapy

### Assessment - primary endpoint

In order to assess the time to incidence of a neurologically confirmed CIPN, a comprehensive **Neurophysiological assessment** that includes the entire symptom pattern of CIPN, is necessary (Table 1):

**Table 1 Tab1:** Flow-chart of assessments

		Baseline T0	T1	Tp	T2	Ti	Status measurement
Time points		Prior to first cycle of therapy	After 3 months	After medical therapy	3 month follow-up	Incidence CIPN	every 6 weeks
Intervention	Training	2 x per week throughout entire medical therapy			Patients offered to continue		
Anamnesis I	Entity, stadium, pre-treatment, pre-diseases, allergies, planed therapy, neurological anamnesis, CIPN relevant medication, social anamnesis	X					
Anamnesis II	Begin of CIPN Symptoms, reception of planed therapy. Amount of cycles, potential change of medication or therapy, CIPN relevant medication			X	X	X	
Anamnesis III	Reception of CIPN relevant medication, therapy of CIPN			Only CG	Only CG	Only CG	
Neurological assessment	Neuroelectrography (NCV, Amp)	X	X	X	X	X	
	Neurological clinical tests battery	X	X	X	X	X	X
Performance status	Static and dynamic postural control	X	X	X	X	X	
Questionnaires	Subjective reduction of symptoms (FACT/GOG-Ntx / EORTC CIPN 20) Quality of life (EORTC QLQ-C 30) Neuropathic pain (PainDETECT and VAS) Level of physical activity (FFKA)	X	X	X	X	X	

*CIPN* Chemotherapy-induced peripheral neuropathy, *CG* control group, *NC*V nerve conduction velocity, *Amp* amplitude, *VAS* visual analogue scale

Nerve conduction studies are performed by trained, certified and blinded examiners. For patients of the University Hospital Cologne as well as the joint practice at Sachsenring, neurophysiological assessments are performed in the Electrophysiology Laboratory of the Department of Neurology, University Hospital Cologne. Patients in Eschweiler are seen by a local neurologist. Assessment methods are standardized and aligned among the investigators. Furthermore, patients are asked not to mention the arm they are participating in to the investigators. Examiners are trained by a gold-standard examiner using a standard operating procedure and certified prior to the study.

#### Nerve conduction studies

For nerve conduction studies, motor and sensory nerves are assessed. Compound muscle action potentials (CMAP), distal motor latency, conduction velocity, and F-waves are obtained from the tibial nerve. The tibial nerve is stimulated at the ankle and popliteal fosse. Antidromic sensory nerve conduction studies are performed in the sural nerve. Sensory nerve action potentials (SNAPs) are recorded from the lateral malleolus with surface electrodes. Skin temperature is monitored and maintained above 32 °C using a heater if necessary.

We furthermore conduct a standardized neurological clinical test battery that is a feasible assessment method for oncological patients in order to check for first neuropathic symptoms. It is used as a pretest to screen for CIPN related symptoms. Should one of the components show irregularities, a neuroelectrography is required in order to detect and document a possible CIPN.

The test battery contains the following assessments:**Peripheral deep sensitivity** is evaluated by the use of a Rydel-Seiffer tuning fork (128 Hz) with a scale from 0 to 8. Due to age related neural deconditioning, values ≤4 are pathological for patients ≥60 years old, while for patients under 60 years old, ≤5 is regarded as pathological [34].**The Reflex action** of the Achilles- as well as the patellar tendon is assessed with a reflex hammer and graded on a 3-point scale (1 = agile, 2 = weak, 3 = missing).**Sense of position** is assessed by asking patients if they can recognize a change of position in their first toe, with their eyes closed.**Perception of touch** is evaluated by symmetrically stroking the outsides of the patients’ legs and feet in order to detect reduced or altered sensation due to demyelination or axonal degeneration [30, 35].**The strength of the lower leg muscles** is assessed by requesting the patient to actively move their legs against the resistance of the examiner’s arm. The examiner then grades the strength on a six-point scale (0 = no activity, 1 = visual contraction without motor effect, 2 = movement under elimination of gravity, 3 = movement under gravity, 4 = movement against slight resistance 5 = normal force).

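### Nerve conduction between the fixed visits is triggered by a clinical battery that training may itself improve, so part of a longer time to confirmed CIPN may be later detection

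*Protocol article*

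**What the plan says.** The abstract (Methods) states: "Primary endpoint is the time to incidence of neurologically confirmed CIPN". The event time is therefore tied to when CIPN is confirmed.

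Table 1 (Assessment - primary endpoint) marks the row "Neuroelectrography (NCV, Amp") at T0, T1, Tp, T2 and Ti, but not in the 6-weekly status column. The clinical battery is marked in all six columns.

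The section Nerve conduction studies describes the battery as tuning fork, tendon reflexes, position sense, touch and lower-leg strength. Of its role it says: "It is used as a pretest to screen for CIPN related symptoms". The rule that follows is: "Should one of the components show irregularities, a neuroelectrography is required in order to detect and document a possible CIPN".

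Experimental design gives the routes to detection between fixed visits:
- "Additionally, a short neurological test battery is performed every 6 weeks"
- "patients are informed about possible symptoms of CIPN and asked to report back to the study coordinators immediately"
- "patients are regularly asked for potential symptoms by their physicians"

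The Background reports effects of exercise on the same signs. In the pilot in patients with confirmed CIPN, both exercise groups had "improved reflex activity of the Achilles- and patella tendon), peripheral deep sensitivity and pain". The earlier lymphoma trial is cited for an 87% reduction of CIPN-related symptoms, with deep sensitivity as the example, against 0% in controls. SMT is credited with better proprioception and WBV with better isometric strength. Potential for bias states that patients know their allocation.

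**The concern.** The gate to the confirming test consists of signs and symptoms that the interventions are expected to improve. Suppose a trained patient and a control patient have the same nerve damage at week 6. If training has improved vibration sense or reflexes, the trained patient may pass the battery and be confirmed only at T1, while the control patient is sent for nerve conduction at once.

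Blinded examiners protect the reading of the test. They do not equalise who is sent for it, or when. The rule that therapists must not ask about symptoms equalises enquiry, not the sensitivity of the battery.

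The Discussion expects training to prevent or postpone CIPN. Under this rule, postponed onset and postponed detection can look alike in the primary analysis.

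**Working it through.** The plan gives no figure for this effect, so there is none to reproduce. The check asks how large an apparent benefit the detection rule could create when true onset is the same in both arms.

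**Inputs from the protocol.** 65 evaluable patients per group; log-rank test, two-sided 5% (2.5% in favour of training); incidence 90% with TAU and 75% with intervention; battery every 6 weeks. The planning hazard ratio is ln(0.25)/ln(0.10) = 0.60.

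**Visit schemes.** 3-month therapy: nerve conduction at weeks 12 (T1 = Tp) and 24 (T2), battery between them at weeks 6 and 18. 6-month therapy: nerve conduction at weeks 12, 24 and 36, battery at 6, 18 and 30. The article does not say whether status visits continue after therapy, so both cases are shown; without them the last battery visit drops out.

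**Assumptions, not in the documents.** The battery catches 80% of existing cases in control and 60% or 40% in a trained arm. Scheduled nerve conduction catches all. True incidence is 90% by T2 in both arms, with onset hazard either constant or rising (Weibull shape 2). Self-report and physician enquiry are left out.

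**By hand, 3-month therapy, constant hazard.** Cumulative onset by week t is 1 − 0.1^(t/24).
- Week 6: onset 1 − 0.1^0.25 = 0.438. Detected: control 0.8 × 0.438 = 0.35; trained 0.4 × 0.438 = 0.18.
- Week 12: onset 1 − 0.1^0.5 = 0.684. Detected: 0.684 in both arms.
- Week 18: new onset since week 12 is 0.1^0.5 − 0.1^0.75 = 0.138. Detected: control 0.684 + 0.8 × 0.138 = 0.79; trained 0.684 + 0.4 × 0.138 = 0.74.
- Week 24: 0.90 in both arms.

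The arms separate between fixed visits and meet again at each one. Cumulative incidence by T2 is unaffected in this model; event times are not. With a rising hazard, onset by week 6 is only 1 − 0.1^(1/16) = 0.134, so the week-6 gap shrinks to 0.107 versus 0.054.

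**Simulation.** 4000 trials per cell, log-rank on detection times, hazard ratio estimated as exp(U/V), where U is the log-rank score and V its variance. Each cell gives the spurious hazard ratio and the share of trials significant in favour of training.

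| Therapy; battery weeks | Onset hazard | Trained 0.6 | Trained 0.4 |
|---|---|---|---|
| 3 months; 6, 18 | constant | 0.88; 7.0% | 0.76; 18.8% |
| 3 months; 6, 18 | rising | 0.89; 6.7% | 0.80; 14.7% |
| 3 months; 6 | constant | 0.90; 5.9% | 0.79; 13.5% |
| 3 months; 6 | rising | 0.96; 3.2% | 0.95; 3.6% |
| 6 months; 6, 18, 30 | constant | 0.93; 5.4% | 0.85; 10.1% |
| 6 months; 6, 18, 30 | rising | 0.94; 5.4% | 0.87; 9.1% |
| 6 months; 6, 18 | constant | 0.93; 5.0% | 0.86; 9.4% |
| 6 months; 6, 18 | rising | 0.97; 3.5% | 0.92; 5.6% |

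With equal sensitivity (0.8 in both arms) the hazard ratio is 0.99 to 1.01 and the rejection rate 1.9% to 3.0%, so the excess comes from the sensitivity gap alone.

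**Scheduled nerve conduction only.** Ignoring the battery visits gives a hazard ratio of 0.99 to 1.01 and 2.2% to 3.0% in favour of training. At a true hazard ratio of 0.60 and equal trigger sensitivity (2000 trials), power in each scenario is within 2.3 percentage points of the trigger-based analysis, in either direction.

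**The case against.** A reader might infer that training masks symptoms while nerve damage proceeds unchanged, so that a positive result would be an artefact. The documents do not support this. The pilot summary reports better signs but does not say whether nerve conduction changed, and the Background credits SMT with regeneration of neuromuscular structures. Better signs may therefore be the treatment effect itself. The pilot also had 10 patients per arm, all with established CIPN, over 6 weeks, which does not show reduced screening sensitivity at first onset. The article says the assessment must cover the whole symptom pattern and gives no electrophysiological case definition for follow-up; the stated cut-offs serve baseline exclusion. If signs belong to the endpoint, preserved signs are partly real delay.

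A reader might also take it as certain that the bias favours training. It is not: twice-weekly supervised contact, or the pain that vibration may provoke in patients with neuropathic pain, could bring reporting forward.

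The trigger is hard to escape, too. One irregular component out of five domains is enough, patient reports and physician enquiry add to it, and everyone has nerve conduction at T1, Tp and T2.

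All of this stands as a limit on size, certainty and direction. It does not remove the mechanism: nerve conduction is the stated means of confirmation, the battery is its screen, and no safeguard makes that screen independent of arm. Nor does the point rest on detail left to an unseen analysis plan, because the detection rule is stated in the article.

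**Conclusion.** The concern holds as a risk of differential timing of detection. Between fixed visits, the confirming test can come at different times by arm at equal nerve damage, and part of a longer time to confirmed CIPN may be later detection. This would probably favour training.

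A battery miss costs about one 6-week interval. A case that relies on self-report could wait up to about 12 weeks for the next scheduled study.

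Under the assumed sensitivities the spurious hazard ratio lies between about 0.97 and 0.76, with false findings in favour of training between about 3% and 19%. The mild end belongs to rising onset with no status visits after therapy, the severe end to constant onset with continued visits and a sensitivity of 0.4. These figures rest on assumed sensitivities and onset patterns and omit the other detection routes, so they show what is possible, not what is expected. None of the scenarios reaches the planning hazard ratio of 0.60.

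**What to change.** Keep the trigger-based primary analysis. Prespecify one supporting analysis:
- Use only the nerve conduction results from the scheduled T1, Tp and T2 visits, in all patients, whether or not they had a Ti test. Do not carry triggered cases forward to the next visit.
- Apply one electrophysiological criterion in all arms.
- Analyse as interval-censored time, with cumulative incidence by T2 alongside.
- Report the hazard ratio and its confidence interval beside the primary result.
- Describe the effect as prevention or delay of nerve damage only if this analysis points the same way. Otherwise describe it as delay of clinically detected CIPN.

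Cost: one extra analysis of data already scheduled, with no new tests or visits. The downside is coarser timing and possibly slightly less power. In 3-month therapy only two post-baseline time points remain, because T1 and Tp coincide.
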